**6. Methods: Monitoring**

**6.1 Data Monitoring**

Given the short duration and minimal risk nature of the study, a formal data monitoring committee is not required. Regular monitoring will be conducted by the steering committee.

**6.2 Harms**

Adverse events related to the EDX procedure itself will be recorded and managed according to standard clinical protocols. The study adds no additional physical risk to patients.

**6.3 Performance Error Analysis**

The study will systematically identify and analyze AI performance errors, defined as:

1. Misclassification of normal vs. abnormal studies
2. Incorrect interpretation of specific findings
3. Inappropriate diagnostic conclusions
4. Missing critical information
5. Technical failures of the AI system

For each error, we will document:

- Type and severity of error
- Potential clinical impact
- Whether the error was detected and corrected by the reviewing physician
- Root cause analysis (technical limitation, data quality issue, etc.)
- Potential solutions or improvements

A dedicated log of performance errors will be maintained throughout the trial and will inform future system improvements. Regular reviews of error patterns will be conducted by the technical team and clinical experts.

**7. Ethics and Dissemination**

**7.1 Research Ethics Approval**

This study has been approved by the Institutional Review Board of Rambam Healthcare Campus.

**7.2 Protocol Amendments**

Any modifications to the protocol will be communicated to the IRB, trial registry, and all study team members. Significant amendments will require IRB approval before implementation.

**7.3 Consent**

Written informed consent will be obtained from all participants by trained research staff prior to enrollment. Participants will be informed that their EDX studies will be used to test an AI system but that their clinical care will not be affected.

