**Abstract**

**Introduction**: Electrodiagnostic (EDX) testing is fundamental for diagnosing neuromuscular disorders. However, interpretation is time-consuming and requires specialized expertise. This trial aims to evaluate whether an AI-assisted approach can improve the accuracy and quality of EDX reports compared with conventional physician-only interpretation.

**Methods and Analysis**: This single-center randomized controlled trial will enroll 200 adult patients scheduled for routine EDX testing at Rambam Health Care Campus, Haifa, Israel between January 21, 2025, and February 21, 2025. Participants will be randomized 1:1 to either AI-assisted physician reporting or standard physician-only reporting. The AI intervention (INSPIRE) is a multi-agent framework built upon ChatGPT-4o large language models hosted on the AZURE AI platform, which will generate preliminary EDX reports for physician review and editing. The primary outcome is report quality, assessed using the AI-Generated EMG Report Score (AIGERS; range 0-1). Secondary outcomes include measures of AI-physician collaboration efficiency and physician satisfaction with the tool. A two-week calibration phase will precede trial initiation to optimize AI integration.

**Ethics and Dissemination**: This study was approved by the Rambam Healthcare Campus Institutional Review Board. Results will be published in peer-reviewed journals and presented at scientific conferences.

**Trial Registration**: ClinicalTrials.gov Identifier: [NCT06902675](https://clinicaltrials.gov/study/NCT06902675)

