**2. Introduction**

**2.1 Background and Rationale**

**2.1.1 Intended Use of the AI Intervention**

The INSPIRE AI framework is intended to assist neurologists in interpreting electrodiagnostic (EDX) tests (including electromyography and nerve conduction studies) and generating diagnostic reports. The primary purpose is to reduce documentation burden, standardize reporting, and potentially improve diagnostic accuracy. The intended users are board-certified neurologists who regularly perform EDX tests in clinical practice.

Within the clinical pathway, EDX studies are conducted to evaluate patients with suspected neuromuscular disorders. Currently, physicians manually interpret the raw data and compose reports, a process that is time-consuming and subject to variation in quality and completeness. The INSPIRE system will generate a preliminary report based on the raw EDX data, which will then be reviewed, verified, and edited by a neurologist before finalization. This is expected to streamline workflow while maintaining or improving diagnostic accuracy.

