**2.2 Explanation for Choice of Comparators**

The control arm (physician-only reporting) represents the current standard of care for EDX interpretation. This comparator was chosen to directly assess whether the addition of AI assistance provides measurable improvements over existing clinical practice. By comparing AI-assisted reporting to standard physician reporting, we can determine the added value of the AI intervention in real-world clinical settings.

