**2.4 Trial Design**

This is a single-center, randomized controlled trial with two parallel arms and 1:1 allocation ratio:

1. Intervention arm: AI-assisted physician EDX report generation
2. Control arm: Standard physician-only EDX report generation

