**3.5 Participant Timeline**

The study will follow a simple timeline:

1. Screening and enrollment prior to scheduled EDX appointment
2. Randomization on the day of the EDX study
3. EDX testing performed according to standard clinical protocols
4. Report generation (either AI-assisted or physician-only)
5. Quality assessment and data collection
6. No follow-up visits required for the study (though patients may have clinical follow-up as determined by their treating physician)

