**4.1.3 Implementation**

The allocation sequence will be generated by a biostatistician not involved in patient enrollment. Research coordinators will enroll participants, and the treating neurologists will assign participants to interventions based on the randomization envelope.

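### The assurance in section 7.3 that clinical care will not be affected does not fit a design that randomises how each patient's own diagnostic report is produced

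*Protocol*

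**What the plan says.** Section 7.3 of the protocol states: "Participants will be informed that their EDX studies will be used to test an AI system but that their clinical care will not be affected".

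The intervention is described elsewhere as follows.

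- The abstract says of INSPIRE, as used in this trial: "which will generate preliminary EDX reports for physician review and editing".
- Section 2.1.1 places the AI in the clinical pathway and says of the draft: "which will then be reviewed, verified, and edited by a neurologist before finalization".
- Section 2.2 calls physician-only reporting the standard of care, makes it the control arm, and says of the comparison: "we can determine the added value of the AI intervention in real-world clinical settings".
- Section 2.4 defines the randomised arm: "Intervention arm: AI-assisted physician EDX report generation".
- Section 3.5 lists one reporting step per participant, worded as an alternative: "Report generation (either AI-assisted or physician-only").
- Section 4.1.3 says who applies the allocation: "the treating neurologists will assign participants to interventions based on the randomization envelope".
- Section 6.3 requires each AI error to be documented, including "Potential clinical impact" and whether the reviewing physician found and corrected it.

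**The concern.** The sentence in section 7.3 reads as if the AI were tested on patients' data alongside their care. The design sections put the AI inside the production of the patient's own report. A diagnostic report is part of clinical care, and the trial exists to find out whether AI drafting changes its quality. If the AI-assisted report is the one that reaches the referring clinician, participants would agree to take part on an assurance that the design does not support, about the very thing that is randomised.

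**Working it through.** There is no arithmetic to reproduce beyond counting who is concerned. The check sets the sections side by side.

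1. **Whose report is it?** Section 3.2.1 enrols patients referred for routine EDX testing. Sections 2.4 and 3.5 randomise these patients to a method of reporting, and section 4.1.3 has their treating neurologists apply the allocation. The randomised object is therefore the report on that patient's own clinical test.

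2. **What becomes of the AI draft?** Section 2.1.1 has a neurologist review, verify and edit it before the report is final. That section describes intended use, but the abstract says the same of the trial itself. Section 3.3.4 adds that the physician reads the draft next to the raw data.

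3. **Is there a second report, made without AI, for patients in the AI arm?** None is described. Section 3.5 has one reporting step, and it is either/or. The only additional version of a report that the analysis uses (section 5.2.2) is the AI draft before the physician's changes. Section 4.2 has reports reformatted for blinded scoring, but does not say which version goes to care.

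4. **Does the protocol itself expect the content of the report to differ?** Yes. The primary objective (section 2.3) is that AI assistance improves report quality. Half of the primary score (section 3.4.1) rates the accuracy and appropriateness of the clinical interpretation. Section 2.1.1 expects diagnostic accuracy to be maintained or improved. Even an effect that is purely beneficial would be an effect on care if this report is used clinically.

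5. **Does the protocol allow for errors that pass review?** Yes. Section 6.3 records, for each AI error, its possible clinical impact and whether the physician detected it. That treats detection as an open question.

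6. **Two readings remain.**
   - *The AI-assisted report is released for care.* Points 1, 2, 4 and 5 then conflict with the unqualified assurance, and section 7.3 must change.
   - *A report made without AI is released for care.* The assurance could then stand, but no section describes that report. Section 3.5 would lack a step, and sections 2.1.1 and 2.2 would need to be reconciled with it.

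   Under either reading some text has to change.

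7. **Who is concerned?** Section 3.6 plans 200 participants, and 200 × 1/2 = 100 per arm. All 200 receive the assurance. The conflict concerns the 100 planned for the AI arm.

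**The case against.** The best defence is that the sentence is imprecise and not wrong. Both arms have the standard EDX examination, a neurologist produces the report in both, the AI draft is read with the raw data at hand, and the study requires no follow-up visits. The sponsor may have meant only that testing and responsibility stay the same. That is a plausible account of the intention, but it does not rescue the wording. Physician review lowers the risk from a wrong draft without making care unaffected, and section 6.3 provides for errors that review misses. IRB approval (section 7.1) does not remove an inconsistency within the text.

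A second part of the defence does stand: no section states which report is released for care. A reader might infer that the assurance is simply false. The documents do not support that as a flat statement, because clinical release of the AI-assisted report is inferred from the pathway description, the either/or step and the absence of any parallel report. The sentence quoted from section 2.2 justifies the comparator and does not settle the matter.

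Some further inferences are tempting but should not be drawn.

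- *That participants are not told of the randomisation.* Section 7.3 is a summary and the consent form is not shown, so its content is unknown.
- *That the number of patients harmed can be read from the 92.2% accuracy in section 3.3.1.* That figure is retrospective, section 2.1.2 says the retrospective study used an older version of the system, and it describes performance before any physician review. The relevant quantity is errors that survive review, and the protocol gives no figure for it.
- *That drafting error is the only risk added.* Processing patient data on a cloud platform is another, with its own safeguards in section 5.1.3.
- *That the monitoring arrangements fall with the consent sentence.* Section 6.2 speaks of physical risk, and section 6.1 argues from short duration and minimal risk. Neither cites the assurance in section 7.3.

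**Conclusion.** The assurance in section 7.3 is not consistent with the design described in the abstract and in sections 2.1.1, 2.4, 3.5, 4.1.3 and 6.3, and these must be reconciled before participants are given it. The finding is that the passages do not fit together as written. It becomes the stronger finding, that participants are given a wrong assurance, only if the AI-assisted report is the one used for care. That is the likelier reading, but it is not stated.

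The size is a count of people and not of errors: 200 participants receive the assurance, and for the 100 planned in the AI arm it conflicts with what the protocol describes. No estimate, test or endpoint is affected. The point rests on the wording of section 7.3 alone and assumes nothing about the unseen consent form. It should be fixed because it concerns what participants agree to, and because the correction is small.

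**What to change.** First settle, in the protocol, which report is released for clinical use in the AI arm. Then take one of two routes.

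- **If the AI-assisted report is used clinically:** replace the assurance in section 7.3 with a statement that in one arm the participant's report is prepared by a neurologist who edits an AI draft, and that the draft may contain errors which the review is meant to catch but may not. Change any matching wording in the consent form.
- **If care is meant to be unaffected:** state that a report made without AI is the one used clinically, add that step to section 3.5, and reconcile sections 2.1.1 and 2.2 with it.

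Which route applies is for the sponsor to say. The first costs about a paragraph, IRB approval of the revised wording under section 7.2, and possibly a few more refusals, and it needs no change to the design or analysis. The second also needs an amendment; if no such parallel report exists today, it adds a second report for each of the 100 patients planned for the AI arm.

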**7.4 Confidentiality**

All participant information will be de-identified for analysis. Data will be stored on secure servers with access limited to study personnel. All team members will complete training in human subjects protection and data security.

**7.5 Declaration of Interests**

All investigators have reported no conflicts of interest related to this study.

**7.6 Access to Data**

The final trial dataset will be accessible to the principal investigators and the data analysis team. Other researchers may request access to de-identified data after the primary analyses are complete.

**7.7 AI Intervention Access**

The INSPIRE AI framework code and model architecture will be made available for research purposes upon request after study completion, subject to intellectual property considerations. Documentation of the system architecture, training methodology, and limitations will be provided alongside any shared code. Access to the actual trained model may be limited by licensing restrictions from the underlying LLM provider (Microsoft Azure).

**7.8 Dissemination Policy**

Study results will be published in peer-reviewed journals regardless of outcome and presented at scientific conferences. Participants may request a summary of the findings. All publications will follow CONSORT-AI reporting guidelines.
